#### Safety outcomes

The safety outcomes, as initially flagged from patient interviews and confirmed with family physicians, are:Major thromboembolic events (including non-hemorrhagic stroke, deep vein thrombosis, pulmonary embolus, and acute arterial occlusion)Major bleeding events (includes all bleeding events requiring hospitalization or transfusion such as hemorrhagic stroke and GI bleeding).

As this study is small, relatively low risk, and of short duration, there will be no interim safety analysis and hence no formal data safety monitoring board.

The occurrence of major adverse events will be reported to the principal investigator, who will determine the appropriate action should a signal of harm in the intervention group arise.

### Sample size

We wish to be able to demonstrate a 20 % reduction in time out of therapeutic range and will conservatively estimate (since there are no prior studies exploring this outcome to guide us) that the standard deviation of this measure is twice the mean effect (i.e., SD = 40 %). For a *t* test with 1:1 allocation to the control and experimental groups, power = 0.9, alpha = 0.05, minimum difference = 20 %, and SD = 40 %, the required sample size per group is 85 (i.e., 170 subjects in total). Providing for potential dropouts, we will increase our target enrollment to 200 subjects.

### Statistical analysis

#### Calculating TTR

The therapeutic INR range for each patient will vary and be determined by the treating physician. Typically the therapeutic range is 1 unit wide (often 2–3 or 2.5–3.5), but some physicians will choose narrower or wider ranges (e.g., 3.0–3.5 or 2–3.5). We will standardize the width of all target ranges by determining the midpoint of each patient’s individual target range and use upper and lower limits that are 0.5 unit above and below this midpoint. For example, if a physician is targeting a narrower than normal 3.0–3.5 range, we will use a midpoint of 3.25 and assume a (standardized width) target therapeutic range of 2.75–3.75. The proportion of time both in and out of therapeutic range will be determined using the linear interpolation method of Rosendaal, which (conceptually) draws a line between sequential INR values no more than 8 weeks apart and assigns a projected INR value to every day in that interval [8].

#### RCT

All analyses will be by intention to treat. The primary analysis of percentage change in time outside of therapeutic range will be by Student’s *t* test if the data appear to be normally distributed or by Mann-Whitney U test if they are not. As percentage change in time outside of therapeutic range can only be calculated for patients for whom the time outside normal range is not zero, this analysis will exclude anyone who was in range 100 % of the time at baseline. The secondary analyses will be by Student’s *t* test or Mann-Whitney U test (for percentage change in TTR, maximum and minimum INR values, and percentage of time spent above and below target range) and by Student’s *t* test or Fisher’s exact test (for both percentages of patients with TTR >75 % and <60 %, and major warfarin-related cardiovascular events). A subgroup analysis of the influence on the intervention of the numbers of days per week that high vitamin K foods are ingested will be carried out looking at an ANOVA analysis of percent change in time outside of therapeutic range according to three possible categories for the number of days per week of consumption of high vitamin K-containing foods (these being less than 2, 2 to 5, and greater than 5 days per week). In the same analysis we will also examine the effect on the intervention of the patient’s global assessment of how variable their consumption of high vitamin K containing foods is. To do this, we will convert the 4-point scale of possible responses into a dichotomous variable that combines the two options indicating the most variable diet and the two options indicating the least variable diet.

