### Randomization and allocation

Upon receiving eligible baseline INR data, consented eligible participants are contacted by a study coordinator via telephone to obtain baseline information presumed to be predictive of TTR. This includes age ≥80 years, hospitalization in the last 6 months, temporary planned discontinuation of warfarin in the last 6 months (e.g., for elective surgery), number of daily prescription medications, <6 months of warfarin use, the self-reported average number of days per week in which high vitamin K-containing foods are consumed, and how variable the participant feels this estimated level of vitamin K consumption is (on a 4-point scale). This study coordinator (who has no clinical patient interactions) then randomizes the participant, using the REDCap^TM^ randomization module to ensure allocation concealment, to intervention or control [5]. Randomization will employ variable blocks of 2 or 4 and will be stratified by the proportion of baseline INR readings within the therapeutic range (<50 %, 50–80 %, >80 %).

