#### Baseline cross-sectional analysis

The effect on baseline TTR of the number of days per week that high vitamin K-containing foods are consumed will be analyzed with multiple linear regression using baseline covariates which include: gender, age ≥80 years, hospitalization in the last 6 months, temporary planned discontinuation of warfarin in the last 6 months, number of daily prescription medications, <6 months of warfarin use, each of the three possible categories for number of days per week consuming high vitamin K-containing foods, and the patient’s dichotomous global assessment of how variable their pattern of vitamin K consumption is.

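### The primary test is picked by how the outcome data look, and the arm comparison adjusts for neither the randomisation stratum nor baseline time out of range: valid but conservative, and less precise than it need be

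*Protocol article*

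**What the plan says.** The primary outcome (Protocol article, Primary outcome) is the percentage change in time outside the target INR range. Under Statistical analysis, RCT, it is compared by Student's t "test if the data appear to be normally distributed or by Mann-Whitney U test if they are not". The text does not say who judges normality, on which data (pooled or by arm) or by what rule. Patients fully in range at baseline are left out, because their percentage change is undefined.

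Under Randomization and allocation, allocation "will be stratified by the proportion of baseline INR readings within the therapeutic range", with cut-points at 50 % and 80 %. A telephone interview is also held "to obtain baseline information presumed to be predictive of TTR". Such variables enter a model only under Baseline cross-sectional analysis, where the effect of vitamin K intake on baseline TTR "will be analyzed with multiple linear regression using baseline covariates". The comparisons of the two arms have no stratum or baseline term.

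Sample size plans for "power = 0.9, alpha = 0.05", a t test, a difference of 20 % and an SD of 40 %, giving 85 per group. For TTR >75 %, TTR <60 % and major events, the RCT section allows either a t test or Fisher's exact test and does not say when each applies.

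**The concern.** Two things are fixed badly.

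- **The hypothesis depends on the data.** A t test compares means, while Mann-Whitney tests whether values in one arm tend to be larger than in the other. The trial is sized for a mean difference of 20 %. If the rank test is run, the primary p-value no longer refers to that quantity. Percentage change divides by a baseline that can be close to zero, so right skew is to be expected and the rank test is the likely outcome.
- **The design factor is dropped.** The stratum is in effect a baseline version of the outcome. Stratified allocation balances it between arms, but an unadjusted test still counts the between-stratum variation as error. The standard error is then too large and the test rejects too seldom.

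At stake are precision the design has already paid for, and a clear statement of what effect the primary analysis estimates.

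**Working it through.** **1. The plan's own figure.** Inputs from Sample size: difference 20, SD 40, alpha 0.05, power 0.90, 1:1. The normal approximation gives n per group = 2 × (1.960 + 1.282)² × (40/20)² = 84.1, so 85; the noncentral t gives 85.03, and 85 per group has power 89.99 %. One-sided alpha would give 69. The stated figure is therefore that of an unadjusted two-sided t test on means.

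**2. The rule when data are normal.** With SD 40, difference 20, 85 per arm and 5,000 simulated trials, reading the visual check as a Shapiro-Wilk test at 5 % (an assumption), the two-step rule had type I error 4.8 % and power 90.5 %. The t test alone had 90.5 % and Mann-Whitney 89.0 %. Here the rule does little harm.

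**3. The rule when data are skewed.** Assumptions, none of them from the documents: 200 patients, beta-shaped time out of range with mean about 35 %, latent baseline-to-follow-up correlation r of 0.3, 0.5 or 0.7, a true 20 % relative reduction, 2,000 trials per scenario. Monte Carlo error is at most √(0.25/2000) = 1.1 points for power and about 0.5 points near 5 %. Skewness of percentage change was about 2 to 2.5, and Mann-Whitney was selected in about 100 % of trials. With a true effect, the two tests disagreed on significance in 16 to 23 % of trials.

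Power (%):

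| Analysis | r = 0.3 | r = 0.5 | r = 0.7 |
|---|---|---|---|
| Percentage change, t test | 37.8 | 46.6 | 68.8 |
| Percentage change, Mann-Whitney (what the rule selects) | 47.4 | 59.6 | 80.3 |
| Percentage change, linear model with stratum | 50.9 | 56.0 | 73.7 |
| Raw change, t test | 61.2 | 72.4 | 90.9 |
| Follow-up on baseline and stratum, zero baselines excluded | 79.9 | 85.6 | 94.5 |
| Follow-up on baseline and stratum, all patients | 81.4 | 86.0 | 95.0 |

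The absolute levels should not be set against the planned 90 %: the simulated SD of percentage change was about 70 to 120 %, not 40 %. Only the contrasts between rows bear on this point.

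**4. Reading the contrasts.**
- Stratum adjustment alone, against the t test: 50.9 − 37.8 = 13.1, 56.0 − 46.6 = 9.4, 73.7 − 68.8 = 4.9 points. Against Mann-Whitney the same model gains 3.5 points at r = 0.3 but loses 3.6 and 6.6 at the higher correlations. A stratified rank test was not simulated.
- Leaving the percentage scale (raw change minus percentage change, t tests): 23.4, 25.8, 22.1 points.
- Adding baseline and stratum to that (last row minus raw change): 20.2, 13.6, 4.1 points.
- Keeping zero-baseline patients (last two rows): 1.5, 0.4, 0.5 points.

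**5. Type I error in the same scenarios.** t test 2.0, 2.7, 3.8 %; Mann-Whitney 2.4, 3.2, 3.4 %; percentage change with stratum 4.8, 4.7, 5.1 %; full model 4.2, 5.0, 4.6 %. The planned tests are conservative, and adjustment restores a level near 5 %.

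**6. Sensitivity to the assumptions.** Two further simulations used other versions of the same kind of assumptions (r = 0.3, 0.5, 0.7).
- With 170 patients, planned-test type I error was 1.5 to 4.1 %; power was 15/26/48 % (t), 36/51/74 % (Mann-Whitney) and 72/81/93 % (full model); stratum adjustment added about 7 to 9 points to the t test.
- With 200 patients, the corresponding figures were 2.8 to 4.2 %; 32/40/65 %, 46/57/82 % and 79/87/96 %; and 2 to 7 points.

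**7. Closed form for raw change.** With equal variances, adjusting for baseline has variance (1 − r²) against 2(1 − r) for change, a ratio of (1 + r)/2. If 85 per arm were needed for raw change, the adjusted analysis would need 85 × 0.65 = 55.3, 85 × 0.75 = 63.8 and 85 × 0.85 = 72.3, that is 56, 64 and 73 per arm. This does not apply exactly to percentage change.

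**The case against.** The strongest defence is that both candidate tests and the rule between them are prespecified, and that a condensed article may leave the normality criterion, the effect estimate and adjusted sensitivity analyses to an SAP that is not shown. That is fair for the details. It does not cover the primary comparison itself, which the article states as an unadjusted test chosen by appearance.

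Several stronger readings are tempting and are not supported:

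- *The two-step rule inflates false positives or invites selective testing.* Neither the normal nor the skewed scenarios showed inflation. If the data are as skewed as assumed, Mann-Whitney is chosen nearly always, which leaves little to select. The article also states that study evaluators are blinded to allocation.
- *The normality check costs power.* Under skew it moves the analysis to the more powerful of the two tests.
- *Baseline is ignored.* It is the denominator of the outcome. What is missing is adjustment for it.
- *Every planned analysis is an unadjusted two-group test.* The RCT section also plans an ANOVA by vitamin K category and dietary variability.
- *A rank test leaves no effect estimate.* Means, medians or a Hodges-Lehmann shift can still be reported. The narrower point stands that the p-value would not test the mean difference used for sizing.
- *The whole gap to the full model is due to missing adjustment.* About half of it or more comes from leaving the percentage scale, which is a question about the endpoint.

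It is also fair to object that regressing follow-up time out of range replaces an outcome for which the article gives a reason. That counts against calling the change mere wording.

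**Conclusion.** The concern holds as one of efficiency and clarity. The tested hypothesis is left to an unspecified look at the outcome data, and the arm comparison omits the stratification factor and any adjustment for baseline. The direction is the same in all scenarios run: type I error about 2 to 4 % (1.5 to 4.2 % at the extremes) and a gain over the planned t test of roughly 2 to 13 points from the stratum alone. The larger gains of the full model mix adjustment with a change of scale. All sizes rest on assumed distributions and correlations from 0.3 to 0.7, since the documents give neither. Nothing here shows a biased estimate or an excess of false positives. This should be changed, but it would not invalidate the trial.

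**What to change.** - **Primary.** Name one analysis in advance. Preferred: a linear model of follow-up percent time out of range on arm, baseline percent time out of range and the three-level stratum, with a robust or bootstrap 95 % CI.
- **Supporting.** Keep percentage change, compared by a stratified rank test (van Elteren). If percentage change must stay primary, use a single prespecified stratum-adjusted test with a stated effect estimate, and drop the choice by appearance.
- **Binary outcomes.** Use logistic regression adjusted for stratum for TTR >75 % and TTR <60 %, and Fisher's exact test for rare events, in place of the present either-or.

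Cost: no new data, since stratum and baseline INR values are already held. It is still more than a wording change. The preferred model puts the estimate on an absolute scale, so the 20 %/40 % sizing statement must be re-expressed and the stated reason for a relative measure revisited. It also keeps the zero-baseline patients whom the RCT section excludes, so the analysis set must be redefined. The article reports recruitment as still open at submission; the change should be documented before any comparison by arm is seen.

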**Methods/design:**

This is a 7-month Prospective Randomized Open Blinded End-point (PROBE) study in which established evening warfarin users (primary care managed Canadian outpatients in the provinces of British Columbia and Alberta) will be randomized to either switch to morning ingestion of warfarin (the intervention) or to continue with evening use (the control). The primary outcome is the percent change in the proportion of time spent outside the therapeutic range of the international normalized ratio (INR) blood test. Secondary outcomes include change in proportion of time spent within the therapeutic INR range (TTR), percentage of patients with TTR >75 %, percentage of patients with TTR <60 %, and major warfarin-related cardiovascular events (including all-cause mortality, hospitalization for stroke, hospitalization for GI bleeding, and deep venous thrombosis/pulmonary embolism). We will also compare whether day-to-day variability in the consumption of high vitamin K-containing foods at baseline affects the baseline TTR in this cohort of evening warfarin users.

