#### Primary outcome

The primary outcome is percentage change in time spent *outside* the family physician’s target INR range for that patient. This primary outcome has been chosen because we believe this is a measure more likely to be shared by patients across a wide range of TTR. It is also the time spent outside of range that contributes more directly to risk of thrombosis and hemorrhage; hence, the change in this measure is more clinically meaningful than the change in TTR itself.

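### The secondary outcome is listed as change in TTR but tested as percentage change in TTR, a baseline-relative quantity that can give a different answer

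*Protocol article*

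**What the plan says.** The Secondary outcomes section of the protocol article opens its list with change in TTR, without the word percentage. The abstract agrees: "Secondary outcomes include change in proportion of time spent within the therapeutic INR range (TTR". The Primary outcome section keeps the two ideas apart. It chooses percentage change in time outside range as primary and says that "the change in this measure is more clinically meaningful than the change in TTR itself".

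The RCT part of the Statistical analysis section then assigns Student's t test or the Mann-Whitney U test "for percentage change in TTR, maximum and minimum INR values", among others. No test is assigned to plain change in TTR, and nowhere does the article say that the two wordings mean the same thing.

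The same paragraph shows what it means by percentage change. For the primary outcome, it says the measure "can only be calculated for patients for whom the time outside normal range is not zero". That restriction makes sense only for a change divided by its baseline value.

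**The concern.** The listed outcome and the tested outcome are different quantities. Change in a proportion is most naturally the follow-up proportion minus the baseline proportion, whereas percentage change divides that difference by baseline. An analyst following the outcome list and one following the statistical section could report different estimates and p-values from the same data, possibly with opposite signs.

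This outcome carries some weight. Aim 1 and the first hypothesis are worded in terms of time in range. The primary analysis leaves out patients who were always in range at baseline, and change in TTR is the listed change outcome that can keep them. It should have one definition, fixed before results are seen.

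**Working it through.** **1. The plan's own figure.** The only sample size calculation concerns the primary outcome: "power = 0.9, alpha = 0.05, minimum difference = 20 %, and SD = 40" %, with "1:1 allocation to the control and experimental groups". Two-sided, n per group = 2 × (1.96 + 1.2816)² × (40/20)² = 84.06, which rounds up to the stated 85. The exact t-test calculation gives 85.03, and power at 85 is 0.900. The figure reproduces. Nothing comparable is given for change in TTR.

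**2. Dependence on baseline.** With B = baseline TTR and F = follow-up TTR, absolute change is F − B and percentage change is 100 × (F − B)/B. For the same 10-point gain:

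| Baseline TTR | Follow-up TTR | Absolute change | Percentage change |
|---|---|---|---|
| 20 % | 30 % | +10 points | +50 % |
| 40 % | 50 % | +10 points | +25 % |
| 60 % | 70 % | +10 points | +16.7 % |
| 80 % | 90 % | +10 points | +12.5 % |
| 90 % | 100 % | +10 points | +11.1 % |

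**3. Direction.** Suppose two morning patients go from 20 % to 40 % and from 80 % to 50 %, and two evening patients with the same baselines do not change. The difference in mean absolute change is (20 − 30)/2 = −5 points. The difference in mean percentage change is (100 − 37.5)/2 = +31.25 %. The sign reverses.

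**4. Zero denominator.** Entry requires at least four evaluable INR results, and the lowest randomisation stratum, below 50 % of readings in range, has no floor. A patient whose baseline readings all lie on one side of the range, with no crossing, has an interpolated TTR of zero and no percentage change. The paragraph deals with a zero denominator for time outside range but not for TTR. The article does not show how often this would occur.

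**5. Power.** The article gives no SD, baseline distribution or correlation for TTR, so all of these are assumptions: correlated beta-distributed baseline and follow-up TTR, mean 55 to 75 %, SD 15 to 25 points, correlation 0.3 or 0.6, 85 per group. Three effects were tried: a 20 % relative reduction in time out of range, a gain of 8 points, and TTR multiplied by 1.12. That makes 24 settings with 1,000 runs each. Baseline TTR was floored at 2 % so that the ratio exists.

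- *t test:* percentage change had less power than absolute change in all 24 settings, by 10 to 35 points.
- *Mann-Whitney U on both forms:* percentage change ranged from 13 points lower to 5 points higher. For the 20 % reduction in time out of range, the effect closest to the protocol's own target, it ranged from about 1 point lower to 5 points higher.
- *Regression of follow-up TTR on arm and baseline TTR:* highest power in every setting, by about 2 to 23 points over the t test on absolute change.

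Two settings with mean 60 %, SD 20 points and correlation 0.6:

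| Effect | t, percentage | t, absolute | Mann-Whitney, percentage | Mann-Whitney, absolute | Regression |
|---|---|---|---|---|---|
| +8 points | 0.57 | 0.82 | 0.77 | 0.83 | 0.89 |
| 20 % less time out of range | 0.66 | 0.84 | 0.81 | 0.82 | 0.93 |

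**The case against.** TTR is itself a percentage, so percentage change in TTR could be loose wording for a change in percentage points, and the zero-baseline exclusion is written only for time outside range. This is possible but less likely, since the same phrase is used in the relative sense earlier in the same paragraph. Even if it is right, one term then carries two meanings in one paragraph and the text still needs correcting.

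A reader might infer that the main harm is lost power. The documents do not support that. The protocol offers Mann-Whitney U as the alternative when data are not normal, a rule it states for the primary outcome. In a separate simulation under similar assumptions, percentage change in TTR failed a normality test in essentially every run. The rank test would then usually apply, and with it the loss is small or absent.

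A reader might also infer that the article defines the outcome in percentage points, or that the relative form drops patients who were always in range. Neither is so. No section mentions percentage points; that is the natural reading of a change in a proportion. And percentage change in TTR can be computed at a baseline of 100 %; it fails only at zero.

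Finally, an unadjusted two-group comparison of absolute change would be valid, so regression goes beyond what the contradiction alone requires. That stands. Regression is recommended for precision.

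**Conclusion.** The concern holds as a mismatch between the listed outcome and the tested variable. The baseline dependence, the undefined value at zero and the possible reversal of sign are arithmetic and need no assumptions about the data. Reading the tested variable as relative rests on the paragraph's own usage and is likely, not certain. The power figures rest wholly on assumed TTR distributions and are secondary.

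The reach is limited to one secondary outcome. The primary outcome and the stated 85 per group are untouched. It should be corrected, but it does not threaten the trial's main conclusion.

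**What to change.** In the RCT part of the Statistical analysis section, replace percentage change in TTR with absolute change in TTR in percentage points, and use the same wording in the abstract and the Secondary outcomes list. Estimate the arm difference by linear regression of follow-up TTR on arm, baseline TTR and randomisation stratum, in all randomised patients with follow-up INR data. With baseline TTR in the model, the arm coefficient is the between-arm difference in change, in percentage points.

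The cost is one sentence in the analysis section and matching words in two other places. Baseline INR results are already collected for eligibility and the stratum is already recorded at randomisation, so no new data are needed and the sample size does not change.

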#### Secondary outcomes

The secondary outcomes are:Change in TTRPercentage of patients with TTR >75 %Percentage of patients with TTR <60 %For those patients with at least one INR value above the therapeutic range, the maximum INR value observedFor those patients with at least one INR value below the therapeutic range, the minimum INR value observedPercentage of time spent above the therapeutic rangePercentage of time spent below the therapeutic rangeMajor warfarin-related cardiovascular events (including all-cause mortality, hospitalization for stroke, hospitalization for GI bleeding, and deep venous thrombosis/pulmonary embolism)

The percentage of patients with TTR >75 % provides the percentage of patients considered to have excellent control, while the percentage of patients <60 % provides the percentage of patients for whom other anticoagulation strategies may be indicated [6, 7]. Maximum and minimum INR values provide a sense of how far out of range patients go, while major warfarin-related cardiovascular events aggregate outcomes that might stem from both inadequate and excessive anticoagulation.

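### Three yes/no secondary outcomes may be tested by either Student's t test or Fisher's exact test, with no rule to choose between them, and neither test uses the baseline TTR the trial already holds

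*Protocol article*

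**What the plan says.** The RCT subsection of the Protocol article gives the secondary outcomes two pairs of tests. Continuous outcomes get Student's t test or Mann-Whitney U. The second pair is Student's t test or Fisher's "exact test (for both percentages of patients with TTR" above 75 % or below 60 %, and it also covers major events. No condition is attached to either pair.

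The only selection rule in the subsection belongs to the primary outcome, which is analysed by Student's t "test if the data appear to be normally distributed or by Mann-Whitney U test if they are not".

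The Secondary outcomes section shows that the second pair concerns yes/no data. "The percentage of patients with TTR >75 % provides the percentage of patients considered to have excellent control", and "the percentage of patients <60 % provides the percentage of patients for whom other anticoagulation strategies may be indicated". Each patient is therefore on one side of a cut-off or the other. Major events form a composite ("including all-cause mortality, hospitalization for stroke, hospitalization for GI bleeding, and deep venous thrombosis/pulmonary embolism") that each patient either has or does not have.

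Under Randomization and allocation, randomisation is "stratified by the proportion of baseline INR readings within the therapeutic range", in three bands. Baseline INR data are also an entry requirement (Inclusion and exclusion criteria). Neither test named for the binary outcomes uses this information.

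**The concern.** An analyst who follows the text exactly can compute two p-values from one table and report either. If they fall on opposite sides of 0.05, the plan supports two conclusions from the same data. Carrying the normality rule over from the primary outcome does not rescue the sentence. Data coded 0/1 never look normal, so the rule would always select Fisher's test and the t test would be named for nothing.

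There is a separate loss of efficiency. Every randomised patient has a baseline TTR, and the trial thought baseline control important enough to stratify on. An unadjusted comparison of proportions discards it, for outcomes that already lose information by being cut at a threshold.

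**Working it through.** **1. The plan's own figure.** The Sample size section gives "power = 0.9, alpha = 0.05, minimum difference = 20 %, and SD = 40" (per cent). Two-sided, with the normal approximation:

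n = 2 × (1.960 + 1.282)² × (40/20)² = 2 × 10.51 × 4 = 84.1, rounded up to 85 per group.

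The stated 85 per group reproduces (noncentral t: 85.03), and so does the inflation 170/0.85 = 200. A one-sided test would need 69, so 0.05 is taken as two-sided. I use 85 per arm as the analysed number and 100 per arm as the enrolment target.

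**2. The two tests on the same table.** For a and b patients with the outcome out of n per arm, the pooled t statistic is

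t = (a/n − b/n) / √(v × 2/n), with v = [a(1 − a/n) + b(1 − b/n)] / (2n − 2), on 2n − 2 degrees of freedom.

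*Events, 5 v 0 at n = 85.* v = (5 × 0.9412)/168 = 0.02801. SE = √(0.02801 × 2/85) = 0.02567. t = 0.0588/0.02567 = 2.29, p = 0.023. Fisher: 2 × C(85,5)/C(170,5) = 2 × 0.0294 = 0.059.

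*TTR >75 %, 51 v 38 at n = 85.* v = (51 × 0.4000 + 38 × 0.5529)/168 = 0.2465. SE = √(0.2465 × 2/85) = 0.0762. t = 0.1529/0.0762 = 2.01, p = 0.046. Fisher: 0.065.

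| Per arm | Counts | t test p | Fisher p |
|---|---|---|---|
| 85 | 4 v 0 | 0.043 | 0.121 |
| 85 | 5 v 0 | 0.023 | 0.059 |
| 85 | 7 v 1 | 0.030 | 0.064 |
| 85 | 51 v 38 | 0.046 | 0.065 |
| 100 | 7 v 1 | 0.030 | 0.065 |
| 100 | 44 v 30 | 0.041 | 0.057 |

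**3. Direction of disagreement.** Over every pair of counts, 75 pairs at 85 per arm and 93 at 100 per arm are significant by the t test only. None is significant by Fisher only.

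**4. Exact type I error at 85 per arm** (binomial enumeration, same true rate in both arms):

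| Common rate | t test | Fisher |
|---|---|---|
| 2 % | 0.034 | 0.003 |
| 3 % | 0.044 | 0.008 |
| 10 % | 0.050 | 0.029 |
| 30 % | 0.050 | 0.035 |
| 50 % | 0.055 | 0.038 |

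At 1 % the t test's error is 0.009. Every Fisher-significant table is also t-significant, so an analyst who always took the smaller p-value would have the t test's error rate and no more.

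**5. How often the choice matters.** The document gives no expected rates, so these are assumed. The verdicts differ in about 1.5-3.6 % of trials with no true difference. For 30 % v 45 % they differ in 6.2 % of trials (85 per arm) or 5.7 % (100 per arm). For events at 3 % v 10 % they differ in about 10.7 % at either size.

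**6. Cost of ignoring baseline.** Assumptions not in the document: time outside range has mean 35 % and SD 20 points, and baseline and follow-up correlate at 0.5-0.7. The protocol's 20 % reduction is applied as a factor of 0.8 on the intervention arm's time outside range. TTR >75 % means less than 25 % of time outside range. On a normal scale the control proportion is Φ((25 − 35)/20) = Φ(−0.50) = 31 %. In the intervention arm the cut-off becomes 25/0.8 = 31.25, giving Φ(−0.19) = 43 %. Simulated power at 85 per arm:

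| Method | Power |
|---|---|
| Fisher's exact test | about 30-34 % |
| t test | about 36-38 % |
| Logistic regression adjusted for baseline | about 41-48 % |

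At an assumed 30 % reduction all powers are higher and the ordering is the same.

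**The case against.** **The t test is not a bad test here.** This stands. A reader might infer that its normal approximation breaks down for rare events and produces false positives. The enumeration does not support that: its error is at or below 0.055 over rates of 1-50 % at 85 per arm, and is conservative at the lowest rates. Much of the disagreement comes from Fisher's conservatism. The fault is the open choice, not the validity of either test.

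**The normality rule could be read across.** The sentences are parallel, and on that reading Fisher's test always applies. The text does not say so, however, and the reading leaves the named t test with no use. The sentence needs correcting either way.

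**An analysis plan not shown may settle it.** It may. But the protocol is not silent: it states a two-way option, which is a choice fixed badly and not a detail left for later.

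**Baseline adjustment is an improvement, not the repair of an error.** This also stands. Unadjusted tests are valid under randomisation, and ignoring the strata does not bias the result. A reader might infer from the stratified randomisation that the unadjusted tests give wrong answers. The document contains no such contradiction, and the loss is one of power.

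**The power figures rest on assumptions.** The mean, SD and correlation are assumed, and the document does not quantify how well baseline control predicts follow-up. A larger effect than the protocol's own 20 % would make every method look better. At 20 %, TTR >75 % is underpowered by all three, and adjustment narrows the gap without closing it.

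**Conclusion.** The point holds as a defect in the secondary analyses. The plan names two tests for three binary outcomes without a rule, and counts that this trial could well produce are significant by one test and not by the other. Relative to Fisher's test, the freedom runs only towards significance. In size it is modest: the verdict differs in roughly 2-4 % of trials with no effect and 6-11 % under the alternatives tried, all with assumed rates. Even choosing the smaller p-value would keep the error rate close to nominal, so the issue is an unfixed conclusion and not gross inflation of false positives.

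Leaving out baseline TTR costs some 10-14 percentage points of power against Fisher's test at the protocol's effect size (about 30-34 % against 41-48 %), under the assumed distribution and correlation. The primary analysis and the sample size are untouched.

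**What to change.** In the RCT subsection, delete Student's t test for the binary outcomes and name one method for each before the data are seen:

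- **TTR >75 % and TTR <60 %:** logistic regression on arm and baseline TTR, with the randomisation stratum included, reporting a risk difference with its confidence interval.
- **Major events:** Fisher's exact test with an exact confidence interval.

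If the investigators prefer to keep the analysis unadjusted, naming one test for all three outcomes is enough to remove the ambiguity. The adjustment is for power.

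The cost is about one sentence of text, slightly more analysis work, and acceptance of a conservative test for rare events. No new data are needed, since baseline INR results are collected for every participant.
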